## Abstract

**Background:**

Most people living with dementia want to remain living in their own homes and are supported to do so by family carers. No interventions have consistently demonstrated improvements to people with dementia’s life quality, functioning, or other indices of living as well as possible with dementia. We have co-produced, with health and social care professionals and family carers of people with dementia, a new intervention (NIDUS-family). To our knowledge, NIDUS-family is the first manualised intervention that can be tailored to personal goals of people living with dementia and their families and is delivered by facilitators without clinical training. The intervention utilizes components of behavioural management, carer support, psychoeducation, communication and coping skills training, enablement, and environmental adaptations, with modules selected to address dyads’ selected goals. We will evaluate the effect of NIDUS-family and usual care on goal attainment, as measured by Goal Attainment Scaling (GAS) rated by family carers, compared to usual care alone at 12-month follow-up. We will also determine whether NIDUS-family and usual care is more cost-effective than usual care alone over 12 months.

**Methods:**

A randomised, two-arm, single-masked, multi-site clinical trial involving 297 people living with dementia-family carer dyads. Dyads will be randomised 2:1 to receive the NIDUS-family intervention with usual care (*n* = 199) or usual care alone (*n* = 98). The intervention group will be offered, over 1 year, via 6–8 video call or telephone sessions (or face to face if COVID-19 restrictions allow in the recruitment period) in the initial 6 months, followed by telephone follow-ups every 1–2 months to support implementation, with a trained facilitator.

**Discussion:**

Increasing the time lived at home by people living with dementia is likely to benefit lives now and in the future. Our intervention, which we adapted to include remote delivery prior to trial commencement due to the COVID-19 pandemic, aims to address barriers to living as well and as independently as possible that distress people living with dementia, exacerbate family carer(s) stress, negatively affect relationships, lead to safety risks, and frequently precipitate avoidable moves to a care home.

**Trial registration:**

International Standard Randomised Controlled Trials Number ISRCTN11425138. Registered on 7 October 2019

## Administrative information

Note: the numbers in curly brackets in this protocol refer to SPIRIT checklist item numbers. The order of the items has been modified to group similar items (see http://www.equator-network.org/reporting-guidelines/spirit-2013-statement-defining-standard-protocol-items-for-clinical-trials/).

**Table Taba:** 

Title {1}	Clinical and cost-effectiveness of a New psychosocial intervention to support Independence in Dementia (NIDUS) for family carers and people living with dementia in their own homes: A randomised controlled trial
Trial registration {2a and 2b}.	International Standard Randomised Controlled Trials Number: ISRCTN11425138 10.1186/ISRCTN11425138
Protocol version {3}	Protocol Version 3 (06/04/2020)
Funding {4}	This work is supported by Alzheimer’s Society (UK) and is being carried out within the University College London (UCL) Alzheimer’s Society Centre of Excellence for Independence at home, NIDUS (New Interventions in Dementia Study) programme (Alzheimer’s Society Centre of Excellence grant (AS-PR2-16-002).

## Introduction

### Background and rationale {6a}

Most people with dementia want to remain living in their own homes and are supported to do so by family carers. In the UK, 61% of people with dementia live in the community [1]. Unfortunately, care at home often breaks down, necessitating a move to a care home, which can be sudden. Challenging or distressing behaviours leading to family carer stress, challenging relationships with home care services, poor self-care, and home safety risks are common reasons for this [2].

NHS England’s Well Pathway for Dementia and other national initiatives stress the importance of promoting independence for people living with dementia [3]. Living well with dementia has been conceptualised as living with quality of life, choice, autonomy, dignity, and as independently as possible. To our knowledge, only two interventions have demonstrated efficacy in enabling people with dementia to remain in their own homes for longer, to date. Both were delivered in the USA, by clinically trained staff. They were individually tailored and goal focussed [4, 5].

In stream one of the NIDUS study, we carried out qualitative interviews [6, 7] and worked with our public and patient involvement (PPI) co-production group and practitioners, to develop the theoretical model underpinning our intervention [8] to support people with dementia to attain goals they and their family carers considered critical to living as well as possible at home. The intervention is fully manualised and modular, so it can be tailored to the needs of each dyad. Modules draw on behavioural management techniques, enablement strategies, communication, carer support, and psychoeducation strategies, with material selected from existing interventions [9–12] and newly developed by the coproduction group. We tested the feasibility of the intervention with 14 people living with dementia/family carer dyads. We found it to be acceptable to participants, and we used these findings to modify the training and intervention booklets in preparation for the full trial, based on feedback from participants receiving the intervention and the researchers delivering it [13].

Our NIDUS-family intervention is delivered to people with dementia and family carers by NIDUS facilitators (graduate psychologists/social researchers with relevant experience but without formal clinical training) with supervision, training, and clinical oversight, so it can be widely implemented and give value if effective.

We originally planned to deliver the NIDUS-family intervention face-to-face to people in their homes; however, just before the trial started, lockdown restrictions due to the COVID-19 pandemic were imposed in the UK. Following discussion with our PPI members and project management team, we adapted delivery to online video or telephone sessions, so participants could continue to receive it until it is deemed safe for researchers to meet with participants face-to-face. We also adapted our intervention content, specifically to signpost to remote rather than face-to-face services, to acknowledge the restricted options for outdoor activity and the stresses of living through the pandemic lockdown. Most psychological interventions (NHS and research) for people living with dementia are being delivered remotely at the time of writing due to the needs for social distancing during the pandemic. This has illustrated the possibilities of remote delivery as well as challenges. Interventions can be potentially delivered in people’s homes very cost-effectively through video calling or over the telephone, and catchment areas can be widened. Not everyone has access to video calling, however, and engaging dyads over telephone alone may be particularly challenging.

Eight-five percent of people asked by the Alzheimer’s Society said they would want to stay at home for as long as possible if diagnosed with dementia [14]. The purpose of our intervention, to increase the time lived at home, and life quality of people living with dementia by supporting them and their family carers, is all the more pertinent in the current climate, with provision of support services diminished by the COVID-19 restrictions [15]. We have selected Goal Attainment Scaling (GAS) as our primary outcome, asking dyads to set goals that reflected what they considered most important in enabling them to live as well and as independently as possible at home. GAS can detect individualised, clinically meaningful outcomes [16], through measuring the extent to which individual patients or their families meet goals that they set. It has been used across many types of interventions and several conditions with heterogeneous outcomes, including dementia [17–19], where it has been the primary outcome in clinical trials [20, 21].

### Objectives {7}

The primary objective of the trial is to evaluate the effect of NIDUS-family and usual care on goal attainment as measured by Goal Attainment Scaling (GAS) rated by family carers, compared to usual care alone, at 12-month follow-up.

The secondary objectives are to evaluate the effect of NIDUS-family and usual care compared to usual care at 12 month follow-up on:
Researcher rated Goal Attainment Scaling (GAS) scores [21, 22]Functional independence (basic and instrumental activities of daily living) as measured by the Disability Assessment for Dementia Scale (DADS) [23].Quality of life of the person living with dementia as measured by the Dementia Quality of Life Scale (DEMQOL) and/or the DEMQOL proxy completed by the family carer [24];Neuropsychiatric symptoms as measured by the Neuropsychiatric Inventory (NPI) [25];Family carer quality of life as measured by the CarerQol [26];Apathy in the person living with dementia as measured by the brief Dimensional Apathy Scale (b-DAS) [27];Family carer anxiety and depression as measured by the Hospital Anxiety and Depression Scale (HADS) [28];Potentially abusive behaviours of family carers as measured by the Modified Conflict Tactics Scale [29];Service use and care costs assessed using the Client Services Receipt Inventory (CSRI) [30];Duration of time living at home (time spent living at home during the study, up to the point of, if they occur, hospitalisation without return home, move to a care home or death).

### Trial design {8}

The trial is a two-armed, parallel group, single masked, multi-site, superiority randomised controlled trial. Randomisation is blocked and stratified by site using a 2:1 allocation ratio (two dyads are randomised to the intervention group for every one dyad randomised to the usual care group).

## Methods: participants, interventions, and outcomes

### Study setting {9}

We are recruiting potential participants via clinicians and research nurses working in NHS Trust memory clinics/older adult mental health services and GP practices based in London, Bradford, Leeds, Hull, Oxfordshire, Buckinghamshire, Kent, Essex, and Surrey and directly via the recruitment database Join Dementia Research and Twitter. Subsequent to protocol amendments made in response to COVID-19 and before study commencement, informed consent, outcome assessments, and intervention delivery are conducted via telephone or video call, depending on individual participant preference; prior to COVID-19 restrictions, we expected that outcome assessments and intervention sessions would be face to face, and if restrictions are lifted and it is safe to do so during our recruitment period (planned: April 2020 to February 2022), we will also offer this option to participants. At time of writing (October 2020), all trial processes have been conducted remotely. A list of study sites can be found here: https://www.ucl.ac.uk/psychiatry/research/mental-health-neuroscience-department/nidus/about-nidus-study/stream-2-nidus-family.

### Eligibility criteria {10}

People living with dementia/family carer dyads who meet the following inclusion criteria will be recruited:

#### People living with dementia

Documented diagnosis of dementia of any type and severityAdults aged 18+ (no upper age limit)Living in their own homes (including sheltered accommodation, where staff are not on site 24 h a day): alone or with othersHave a family carer/friend willing to participate in the study who is in regular (at least weekly face-to-face or telephone) contact with them;

#### Family carers/friends

Family member or friend of the person living with dementiaHave at least weekly face-to-face or telephone contact with the person living with dementia (not necessarily living with them)English speaking

People will be excluded from participation in the study if they meet any of the following criteria:

#### People living with dementia

Receiving palliative care support and considered to be in the last 6 months of their lifeCurrently enrolled in another intervention trial/research study

#### Family carers

Lack capacity to consentCurrently enrolled in another intervention trial/research studyUnable to identify three goals that support living well/independence at home and within the intervention remit at baseline

### Who will take informed consent? {26a}

Trained researchers will assess capacity to consent. They will obtain verbally-recorded or written informed consent (by post after phone or video call discussion; or face to face if COVID-19 restrictions allow) from each family carer and person living with dementia prior to participation, following adequate explanation of the aims, methods, anticipated benefits, and potential hazards and burdens of the trial. Consent will be sought at least 24 h after potential participants have been given the study documentation. The researcher will explain that participants are under no obligation to enter the trial and that they can withdraw at any time during it, without having to give a reason. Family carers of people who lack capacity to consent will be asked to complete a consultee declaration form on behalf of their relative with dementia.

### Additional consent provisions for collection and use of participant data and biological specimens {26b}

We will not collect biological specimens from participants, so this section does not apply.

### Interventions

#### Explanation for the choice of comparators {6b}

Participants randomised to the control group will continue to receive usual care from NHS memory services, GP practices, and any other health and social care services during the trial period. The Quality and Outcomes Framework (QOF) recommends the development of dementia care plans that address physical and mental health, communication arrangements with secondary care, and identification of a carer in primary care and a face-to-face review every year; in practice, around half of people living with dementia in the UK have a documented annual review [31].

#### Intervention description {11a}

The intervention is delivered over a 1 year period: 6–8 manualised sessions within the first 6 months, by video call/telephone (with potential for face to face when COVID-19 restrictions permit), followed by catch-up calls every 1–2 months (at preference of participating dyad) to review progress towards goals and troubleshoot any difficulties for the remainder of the intervention period. The manualised sessions are tailored to participant’s preferences and needs for staying independent at home. In session one, the facilitator explores the participant’s identified goals and maps them to a menu of training modules, based on their priorities and concerns around maintaining independence at home. They also explore their support networks and identify gaps, sign-posting participants to existing resources and services. The modules include information and strategies addressing the following areas:
Accepting care, arranging, and planning for the futureCommunicating with people living with dementia, family, and professionalsManaging behaviours and challenging behavioursManaging physical health conditionsExercise, activity, and mobilityManaging low mood, anxiety, and apathyCarer wellbeing and supportSafety, environment, telecare, strategies supporting functioning at homeRelaxation and stress management strategiesSleep, diet, and healthy routines

Each of these modules, if selected, is completed over 1–3 sessions; so, we anticipate most dyads will have the opportunity to complete between 2 and 4 modules. At the final appointment (the 6th, 7th or 8th session depending on the needs and preference of the dyad), the facilitator brings together old and new strategies that have worked to help the participant formulate a final action plan. They then conduct telephone calls every 1–2 months to offer support and guidance on implementing strategies and to troubleshoot any problems. Sessions are delivered to family carers and people living with dementia together or to the family carer alone. This is agreed with each dyad (depending on their goals and circumstances) so that the most appropriate arrangement is made for each session for each dyad.

The University College London (UCL) and University of Bradford (UoB) employed facilitators have been trained to deliver the NIDUS-family intervention to people living with dementia at home and their family carers. The intervention delivery training is provided by members of the research team (including an old age psychiatrist (CC), clinical psychologists (MP/PR) and the trial manager (AB), and research network volunteers from the Alzheimer’s Society (MO, DS). Initial training took place over 9 days face to face between January and March 2020. Taught content included clinical skills, taught by a clinical psychologist, with most of the time spent role-playing the sessions to practice delivery and troubleshoot scenarios that might arise. Role plays were conducted within the UCL/UoB research teams, and facilitators also role played sessions with PPI representatives with experience of caring, who then gave feedback to the research team. Facilitators were signed off to deliver the first intervention session, subsequent intervention sessions, and the final intervention session using written sign off sheets completed by members of the research team delivering the training. Facilitators attend group supervision with a qualified clinical psychologist every two weeks and can access individual support between formal supervision sessions if needed.

#### Criteria for discontinuing or modifying allocated interventions {11b}

The intervention has been modified in response to feasibility testing in a previous study [13], and therefore, no further modifications to the intervention are planned. The intervention is currently being delivered online/by telephone as opposed to face-to-face in response to restrictions imposed by the COVID-19 pandemic to ensure participant and facilitator safety. The psychosocial intervention has been assessed as low risk; therefore, we have not set criteria for discontinuation; however, participants may decide to discontinue the intervention sessions or withdraw from the project at any point. If participants decline the intervention at any point, they will be asked if they would still wish to meet with the researchers completing outcome assessments. Although it will be stressed that participants can withdraw at any time without giving a reason, any assessments that have been collected to that point will be retained and contact with participants will be maintained unless researchers are told otherwise. All contacts with participants and reasons for withdrawing from the intervention or study will be documented on the study database.

#### Strategies to improve adherence to interventions {11c}

We are flexible in terms of delivery; this may enable a subject to participate who would like to manage the time commitment the intervention requires—for example by sending material in advance and holding a session of reduced length or combining two sessions into one longer session where this is preferred by the participant. Should a family carer withdraw from the intervention, we will explore the possibility of involving a second family carer, and, if they are eligible and willing, we would consent them into the trial and invite them to complete the primary outcome (GAS) and other proxy complete follow-up questionnaires, but not the follow-up questionnaires that relate to family carer wellbeing. We will record and report where these adaptations are made to support retention of participants in the trial. Facilitators will receive guidance in the form of intervention protocols and manuals. Throughout the trial, facilitators will be supervised to ensure adherence to protocol, with weekly update and monitoring meetings. Audio recordings of 20% of intervention appointments will be used to assess fidelity to the intervention manual, and details of how these will be rated are below.

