#### Primary outcome

The primary outcome is functioning of the person with dementia assessed using family carer rated Goal Attainment Scaling (GAS) at 12 months follow-up. GAS is valid, reliable, and responsive to change in function in people with dementia living at home up to 12 months [21, 22]. Trained researchers will work with family carers and people living with dementia to set SMART (Specific, Measurable, Achievable, Realistic and Time-bound) goals across domains including: cognition, instrumental activities of daily life/self-care, mood, behaviour, and mobility. Family carers will evaluate ‘performance’ of the person living with dementia (or carer wellbeing if the goal relates to this) on a minimum of three and maximum of five goals set at baseline, on a 5-point scale ranging from ‘much worse’ to ‘much better’ than expected. As people will have different goals and numbers of goals, a summary formula standardises the degree of goal attainment [21], analysed as a change score. We will calculate GAS for people with dementia who have died, using procedures outlined by Gordon et al. [32]. Where death was unexpected, attainment in each domain will be rated as − 2. Where death was expected (we exclude clients who are considered to be in their last 6 months of life, but circumstances can change and we follow-up clients for 1 year), goals will be rated as achieved prior to death.

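### The second-carer rule for the primary GAS rating is triggered by withdrawal from the intervention, so retention and change of rater can differ by arm

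*Protocol article*

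**What the plan says.** All references are to the protocol article.

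- **Trigger.** The section on strategies to improve adherence {11c} states: "Should a family carer withdraw from the intervention, we will explore the possibility of involving a second family carer".
- **What the second carer does.** If eligible and willing, "we would consent them into the trial and invite them to complete the primary outcome (GAS) and other proxy complete follow-up questionnaires". Questionnaires on family carer wellbeing are excluded.
- **Purpose and handling.** "We will record and report where these adaptations are made to support retention of participants in the trial".
- **Control arm.** "Participants randomised to the control group will continue to receive usual care from NHS memory services, GP practices" and other services (section {6b}). There is no trial intervention in this arm.
- **Participants who decline the intervention.** Under section {11b}, "they will be asked if they would still wish to meet with the researchers completing outcome assessments".
- **Primary outcome.** "The primary outcome is functioning of the person with dementia assessed using family carer rated Goal Attainment Scaling (GAS) at 12 months follow-up". Goals are set at baseline, and a goal may concern the carer rather than the person with dementia: "or carer wellbeing if the goal relates to this".
- **General retention measures.** Section {18b} lists a choice of video or telephone contact and vouchers. It does not mention a second carer.

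**The concern.** Carer-rated GAS is a judgement made by someone who knows the allocation, since section {17a} says participants cannot be blinded. Who makes that judgement, and whether it is made at all, should be settled in the same way in both arms. Here the rule that settles it depends on an event that, as worded, can occur in one arm only.

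Three things follow.

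1. A primary outcome that would have been missing may be recovered under the intervention, with no stated equivalent under usual care.
2. Some intervention ratings may come from a person who was not the carer recruited with the dyad and who joined after the goals were set.
3. Non-adherence to sessions, which the intention-to-treat comparison is meant to disregard, can influence who supplies the outcome.

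The rule also leaves two gaps: which carer rates when both are available, and who scores goals about the original carer's own wellbeing.

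**Working it through.** **Step 1. Is the trigger specific to one arm?** Section {11c} conditions on withdrawal from the intervention. Section {6b} gives controls usual care alone, so the condition cannot be met there. Section {18b}, where a general rule would be expected, has none. The text does not expressly exclude controls, but nothing in it extends the rule to them.

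**Step 2. Do {11b} and {11c} fit together?** Under {11b}, stopping the intervention leads to a question about continuing outcome assessments, so GAS need not be missing. Under {11c}, the same event may bring in a second carer who is invited to complete GAS. Neither section says which rating is used if the original carer is still willing.

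**Step 3. Is the exclusion of wellbeing measures complete?** Section {11c} keeps second carers off the carer-wellbeing questionnaires. The Primary outcome section allows GAS goals about carer wellbeing, and {11c} gives GAS to the second carer without exception.

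**Step 4. Reproduce the planned precision.** Inputs from section {14}: effect 0.5 SD, two-sided 5%, 90% power, ICC 0.05, cluster size 20 in the intervention arm, 15% loss, 198 + 99 dyads.

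- Design effect = 1 + 19 × 0.05 = 1.95.
- Control n = ((1.960 + 1.282)/0.5)² × (1 + 1.95/2) = 83.0. Intervention n = 166.0.
- Divided by 0.85: 97.7 and 195.3, so 98 + 196 = 294. This is close to the stated 297.
- Analysed numbers: 198 × 0.85 = 168.3 and 99 × 0.85 = 84.15.
- SE = √(1.95/168.3 + 1/84.15) = 0.153 SD. Power = 90.4%.

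**Step 5. Effect of a rater difference (assumed inputs).** The document gives neither a replacement rate nor a difference between raters. Bias b = share of analysed intervention ratings replaced × mean difference between raters. Type I error = Φ(−1.96 + b/SE) + Φ(−1.96 − b/SE). Power if the shift acts against the intervention = Φ((0.5 − b)/SE − 1.96).

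| Share replaced | Rater difference (SD) | b (SD) | % of 0.5 SD | Type I error | Power if against |
|---|---|---|---|---|---|
| 5% | 0.5 | 0.025 | 5 | 0.053 | 87.3% |
| 10% | 0.5 | 0.05 | 10 | 0.062 | 83.6% |
| 5% | 1.0 | 0.05 | 10 | 0.062 | 83.6% |
| 10% | 1.0 | 0.10 | 20 | 0.100 | 74.2% |

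Over a wider range (5–15% replaced, 0.25–1.0 SD), b runs from 0.0125 to 0.15 SD.

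**Step 6. Effect on missingness (assumed inputs).** Suppose loss would be 15% in both arms and a fraction r of intervention losses is recovered. Intervention loss = 15% × (1 − r), and ratings recovered = 198 × 0.15 × r.

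- r = 25%: about 7 recovered; loss 11.3% against 15% in control.
- r = 50%: about 15 recovered; loss 7.5% against 15%.
- r = 100%: about 30 recovered; loss 0% against 15%.

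Steps 5 and 6 should not be run together on one percentage. A replacement changes missingness only if the original carer would not have rated.

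**The case against.** The best defence is that the provision is conditional, probably rare, and serves intention to treat by seeking outcomes from dyads who stop sessions. It sits under the SPIRIT adherence item, which explains why it speaks of the intervention, and its stated aim is retention in the trial generally. Replacements will be recorded and reported. Researcher-rated GAS, and GAS from the person with dementia where able, offer a cross-check. The article condenses a fuller protocol, and analysis detail is left to a separate plan.

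Much of this stands, and it rules out several stronger readings that a reader might draw:

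- **That a control dyad whose carer stops is lost.** The text does not say so. Section {11b} says contact is maintained unless researchers are told otherwise, without limiting this to one arm. What can be said is that no replacement route is stated for controls.
- **That the second carer displaces an original carer who would still rate.** Section {11c} is silent on this, and the second carer can be read as a fallback. It is an ambiguity to be resolved.
- **That the new carer is more engaged and so favours the intervention.** The text requires only eligibility and willingness. The direction of any shift is unknown.
- **That recovering ratings must widen the gap in missingness.** If the intervention arm would otherwise lose more dyads, recovery would narrow it.
- **That the intention-to-treat comparison is broken.** Groups are still compared as randomised. The problem is one of ascertainment and measurement.

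The defence does not remove the arm-specific trigger. Recording replacements makes them visible but leaves the ratings obtained under different rules. The secondary GAS ratings do not change how the primary one is obtained. The absence of a sensitivity analysis from the article is not a fault, since the analysis plan may contain one.

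**Conclusion.** The point holds as a flaw in a stated rule of trial conduct. As worded, the route to a second rater of the primary outcome exists in one arm only; precedence between original and second carer is not fixed; and the exclusion of wellbeing measures stops short of wellbeing goals within GAS.

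Its size and direction cannot be determined from the document. The range of 0.025–0.10 SD rests wholly on the assumed 5–10% replacement and 0.5–1.0 SD rater difference. The upper end requires every replaced rating to differ by a full SD on average, which is extreme. At the lower end the effect on error rates is slight. A change is recommended because it is cheap and removes an avoidable difference between arms; no material bias has been shown.

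**What to change.** Replace the sentence in section {11c} with one rule that covers both arms, and cross-refer to it from {11b} and {18b}:

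- a second carer is sought as outcome rater only when the original carer is unavailable for outcome assessment, whichever arm the dyad is in;
- the original carer remains the GAS rater whenever willing, including after stopping sessions;
- a second carer does not score goals about the original carer's wellbeing, and the handling of those goals in the summary score is stated.

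This concerns only who rates. Whether another carer joins the sessions is a separate matter of intervention delivery.

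A useful addition, if the analysis plan does not already have it, is a sensitivity analysis of the primary outcome with second-carer GAS ratings set to missing, and replacement counts reported by arm.

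The cost is a short amendment, one extra analysis and a few more contacts to find second carers in the control arm. The sample size stays at 297.
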